### Sample Size Calculation

To answer the research question described above, we aim to include 130 participants. That is to statistically detect a medium effect of (Cohen's d) *d* = 0.60, with a power (1–β) of 80% and an α of 0.05 (two-tailed test) for an intention-to-treat analysis using G^*^Power (75). The estimated effect of (Cohen's d) *d* = 0.60 is based on recent meta-analyses on the effects of treatments on internet addiction which shows rather high effect sizes for CBT (16) as well as several other psychological treatments (76).

## Discussion

The aim of this two-armed randomized controlled trial is to evaluate the efficacy of a newly developed internet- and mobile-based intervention for IUD in comparison to a WCG. It is hypothesized that the intervention decreases symptoms of IUD in the intervention group as compared to the WCG.

IUD is associated with a high disease burden, a decline in quality of life, and substantial comorbidities. Yet, treatment options are very scarce and unspecialized (15). This study provides some of the first guidelines for the development and efficacy of internet-based treatment for IUD. The intervention is designed as a low-threshold approach and adapted to various internet activities as part of IUD, comorbidities and cultural backgrounds through testimonials. Though treating IUD with the internet appears contradictive at first, it bears great potential because affected individuals are addressed in their online setting. An internet- and mobile-based intervention is easily accessible, anonymous, therefore likely to lower the threshold of treatment utilization and thus can be attractive to the target group which is usually characterized by low treatment motivation. Furthermore, to create an engaging and motivating intervention, adaptable content and multiple elective components of motivating and educative nature are used. The intervention structure is set up easy to follow and individual tailored. Content tailoring allows participants to make real-time choices, which trigger different content based on preference or need. To account for the quality of the intervention, participants are provided guidance by an eCoach. Besides the supportive and engaging function of the eCoach within the treatment process, guidance also has been shown to increase adherence rates in internet-and mobile-based interventions (26). To increase treatment adherence, eCoaches send participants feedback on completed sessions and are available for consultation. Moreover, we seek to foster the transfer of strategies into daily life, e.g., by sending tiny tasks via app. A strength of our treatment approach is that the intervention aims at reducing internet use and foster a controlled internet usage instead of establishing abstinence. Participants are invited to define their treatment goals on their own and decide about the way they want to change their internet use and how much time they allow themselves to use the internet. Thus, we aim to set up and motivate individuals into a therapeutic process involving participants and fostering self-determination. Further strengths of the study include the strong methodology of a randomized controlled design compromising an appropriate statistical analyses plan with missing data handling with state of the arts methods (77). Thus, this study will contribute significantly to the literature and empirically tested treatment for IUD because, to the best of our knowledge, it is the first study to investigate the efficacy of a guided internet- and mobile-based intervention for the treatment of IUD.

This study also has some limitations. The power analyses was calculated with an estimated effect of *d* = 0.60. It should be taken into account that smaller effects can be clinically relevant as well. We will not include any additional objective measurement of IUD, e.g., tracking of time spent online. To allow a low-threshold approach, only self-reported measurements are used. Future research should consider additional objective measures and independent ratings of internet use and of symptoms associated with IUD. As motivation for treatment is typically low in the target group and guided internet- and mobile-based interventions require high levels of self-regulation, we account for drop-out with a systematic adherence protocol including reminders via email after 7, 14, and 21 days in case participants do not complete a measurement point followed by telephone calls. Moreover, we provide monetary incentives for completing the online questionnaires. With regard to the pitfall of a usually overeducated sample of participants in internet- and mobile-based interventions, we aim to recruit at a broad level in the population, including health insurance companies, counseling centers and local community centers.

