## Abstract

**Context:** Internet Use Disorder (IUD), characterized as the inability to control one's internet use, is emerging as an increasing societal concern as it is associated with reduced quality of life and mental health comorbidities. Evidence-based treatment options are, however, scarce due to the novelty of the diagnosis. Internet- and mobile-based interventions may be an effective means to deliver psychological treatment to individuals with IUD as they address individuals affected in their online setting. The aim of the study is to evaluate the efficacy of a newly developed, guided internet- and mobile-based intervention for IUD.

**Methods:** In a two-armed randomized controlled trial (*N* = 130), individuals showing problematic internet use patterns (Internet Addiction Test ≥ 49) will be randomly allocated to the internet- and mobile-based intervention or a waiting control group. Assessments will take place at baseline, 7 weeks, 6- and 12 months after randomization. The primary outcome is internet addiction symptom severity (IAT) at 7 weeks. Secondary outcomes include quality of life, depressive symptoms, anxiety, and other psychosocial variables associated with IUD.

**Intervention:** The intervention consists of seven sessions: Goal setting and motivational interviewing, impulse control, problem solving, cognitive restructuring, self-worth, relapse prevention, and a booster session. Participants are supported by an eCoach who provides individual feedback after completion of each session. Participants can choose between several elective sessions based on individual need.

**Conclusions:** This is the first study to evaluate an internet- and mobile-based intervention for IUD, which could be a promising first step to reduce individuals' disease burden.

**Trial Registration:** DRKS00015314.

The study is currently ongoing. First participants were enrolled in the study on September 14th 2018. Recruitment will continue approximately through March 2020.

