### Outcomes

#### Primary Outcome

In order to assess the effect of the treatment on symptoms of IUD, the Internet Addiction Test [IAT; (7)] is administered. The IAT is a widely accepted and validated testing instrument that examines a variety of symptoms of internet dependency (29). The 20 items assess, on a 5-point Likert Scale (1 = “rarely,” 2 = “occasionally,” 3 = “frequently,” 4 = “often,” 5 = “always”) the participant's preoccupation with the internet (e.g., “How often do you block out disturbing thoughts about your life with soothing thoughts of the internet?”), excessive use (e.g., “How often do you lose sleep due to late-night logins?”), neglection of work and social life (e.g., “How often does your job performance or productivity suffer because of the internet?”, “How often do you form new relationships with fellow on-line users?”), anticipation (e.g., “How often do you find yourself anticipating when you will go online again?”), and loss of control (e.g., “How often do you try to cut down the amount of time you spend on-line and fail?”). In several studies, the scale has been shown very good internal consistencies (α = 0.91, α = 0.89) (30).

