#### Secondary Outcomes

##### Compulsive internet use

The Compulsive Internet Use Scale (CIUS) (31) consists of 14 items, which refer particularly to the compulsive and impulse control elements of internet use, assessing the severity of symptoms on a 5-point Likert Scale. In several studies, the CIUS has proven to be a valid instrument and has shown good internal consistency (α = 0.89) (32). The scales include withdrawal symptoms, loss of control, preoccupation/salience, conflict (referring to social and work life) and coping (using the internet to cope with stressors).

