##### Depressive symptoms

Self-reported depressive symptoms will be measured with the Patient Health Questionnaire (PHQ-9) (33). This frequently used self-report instrument consists of 9 items that are answered on a 4-point Likert scale referring to the previous 2 weeks. Total scores range from 0 to 27. The internal consistency of this measure has been found to be excellent (α = 0.83–0.92) (34).

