##### Quality of life

To measure quality of life, we will use the Assessment of Quality of Life Instrument (AQoL-8D) (50, 51), which consists of 35 items with eight dimensions: independent living (α = 0.9, ICC = 0.86), pain (α = 0.85, ICC = 0.86), senses (α = 0.69, ICC = 0.51), mental health (α = 0.84, ICC = 0.89), happiness (α = 0.85, ICC = 0.90), coping (α = 0.80, ICC = 0.79), relationships (α = 0.73, ICC = 0.88), self-worth (α = 0.85, ICC = 0.81) (51). Psychometrics properties have been shown to be acceptable.

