### Statistical Methods

Data will be analyzed on an intention-to-treat basis including all participants who will be randomly assigned to conditions. Additionally, study completer analyses including only participants who filled out the questionnaires and intervention completer analyses including only participants who have completed at least four out of six sessions will be conducted. Missing data will be handled using multiple imputations (MIs) calculated by a Markov Chain Monte Carlo multivariate imputation algorithm of 100 estimations per missing value. MI is especially robust with respect to missing data. We will conduct an ANCOVA to examine differences in the primary outcome. To detect differences between the two study groups, we will conduct univariate analysis of covariance to compare secondary outcomes at post-treatment and 6- and 12-month follow-up adjusting for baseline scores. Predictors and mediators of changes of the primary outcome will be analyzed on exploratory basis using linear regression. For all analyses on continuous measures, Cohen's d (74) will be calculated by standardizing the differences between baseline and follow-up scores by the pooled standard deviation of the baselines scores.

The response rates will be compared across conditions with the help of contingency tables and Chi-Squared tests. For primary analysis, significance levels will be set at 0.05, one-sided. For the explorative analysis of the data, the significance levels will be set to 5%. All analyses will be performed with IBM SPSS v. 24.

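### Reminders, calls and incentives are aimed at the whole 7-week questionnaire set; offering the IAT alone at the end of the sequence is a cheap way to replace some imputed primary outcomes with observed ones

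*Protocol article*

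**What the plan says.** The Abstract fixes the primary endpoint: "The primary outcome is internet addiction symptom severity (IAT) at 7 weeks". The Primary Outcome section describes the instrument: "The 20 items assess, on a 5-point Likert Scale". Table 3 schedules it at T2 (7 weeks) together with twelve other questionnaires, the longest being the AQoL-8D, "which consists of 35 items with eight dimensions".

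The handling of non-response to assessments is in the limitations paragraph of the Discussion. After noting that motivation is typically low in this population, the article plans "reminders via email after 7, 14, and 21 days in case participants do not complete a measurement point followed by telephone calls". It adds: "Moreover, we provide monetary incentives for completing the online questionnaires". Both measures refer to the assessment as a unit, and neither singles out the IAT. The reminders in the Guidance section are a different matter, since they concern unfinished intervention sessions.

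Under Statistical Methods, all randomised participants are analysed and missing values are filled by multiple imputation with 100 estimations per value. A study-completer analysis is added.

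**The concern.** The effort to avoid missing data is directed at a long battery in which the primary outcome is about one item in eight. Some participants may be willing to answer 20 questions but not 165. As described, the reminder sequence has nothing shorter to offer them when they decline the full set.

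All outcomes are self-reported, and the Discussion states that no objective measure of internet use is taken. A participant who returns nothing at 7 weeks therefore leaves no other 7-week measure of internet use, and the IAT must be imputed. If non-return is related to the unseen score, imputation under the usual missing-at-random assumption does not remove the resulting bias. An observed score does not need that assumption.

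**Working it through.** **1. Length of the T2 assessment.** Item counts are those stated under Outcomes, for every instrument ticked at T2 in Table 3:

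IAT 20 + CIUS 14 + PHQ-9 9 + GAD-7 7 + AUDIT-C 3 + ISI 7 + PSWQ-3 3 + procrastination scale 9 + KFG 20 + WHO-5 5 + AQoL-8D 35 + WLQ 25 = 157. Adding the CSQ-8 (8 items) gives 165.

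The CSQ-8 asks about satisfaction with the intervention, so controls may not receive it. IAT share: 20/165 = 12.1%, or 20/157 = 12.7%.

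**2. The plan's own sample size.** Inputs from Sample Size Calculation: d = 0.60, 80% power, two-sided α = 0.05. Allocation is 1:1, so N = 130 means 65 per arm. A two-sample t-test needs 44.6, rounded up to 45 per arm, N = 90. The stated 130 is not reproduced from these inputs; that is a separate matter. What counts here is that 65 per arm gives two-sided power of 0.924 at d = 0.60 with complete data, so there is room for some loss.

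**3. Effect of an IAT-only request.** The article gives no non-response rate and no rate at which a short form would recover people. Both are assumptions: missing share m = 15%, 25% or 35%; recovered share of the missing r = 0, 1/4 or 1/2.

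- Imputed share after recovery = m(1 − r).
- Observed per arm, n = 65 × [1 − m(1 − r)].
- Power from the noncentral t distribution with noncentrality 0.60 × √(n/2), two-sided α = 0.05, observed cases only.

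| m | r | Imputed share | Observed IATs of 130 | Power, d = 0.60 |
|---|---|---|---|---|
| 15% | 0 | 15% | 110.5 | 0.88 |
| 15% | 1/4 | 11.25% | 115.4 | 0.89 |
| 15% | 1/2 | 7.5% | 120.2 | 0.90 |
| 25% | 0 | 25% | 97.5 | 0.83 |
| 25% | 1/4 | 18.75% | 105.6 | 0.86 |
| 25% | 1/2 | 12.5% | 113.8 | 0.89 |
| 35% | 0 | 35% | 84.5 | 0.78 |
| 35% | 1/4 | 26.25% | 95.9 | 0.83 |
| 35% | 1/2 | 17.5% | 107.2 | 0.87 |

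Example, m = 25% and r = 1/4: 0.25 × 0.75 = 0.1875; n = 65 × 0.8125 = 52.8; noncentrality 0.60 × √26.4 = 3.08; power 0.86.

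Observed-case t-test power is only a rough guide. The planned ANCOVA and the imputation would both change it, and the calculation says nothing about bias.

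**The case against.** A reader might infer that anyone who refuses the length also loses the primary outcome. The article does not support this. It does not give the order of the questionnaires, say whether partial answers are stored, or say what the telephone calls ask. Table 3 lists the IAT directly after demographics, which is compatible with asking it first, although the table does not state an order of administration. If the IAT comes first and is saved, a participant who stops midway still supplies it. The short form would then help only with people who never open the set. Such details are commonly left to a full protocol, and their absence from an article is not a defect. This part of the objection stands, and no claim is made about order or saving.

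It is also fair to say that the plan already has three e-mails, telephone calls, payment and multiple imputation, and that nothing here is contradictory. Non-response may come from lost interest or lost contact rather than length, in which case a short form recovers few. The article speaks of low motivation for treatment, not of reluctance to fill in long questionnaires. The recovery rates are therefore unsupported by the document. Nor is power in trouble: at the planned effect with 25% missing it already exceeds 80%, and on the one-sided test named under Statistical Methods it is about 0.90.

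What remains is narrower. The article does describe its retention effort (intervals, channel, escalation, incentive), and that effort is aimed at the whole assessment. Giving it a last step aimed at the primary outcome is a concrete improvement that does not depend on the silent details.

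**Conclusion.** This is a low-severity, inexpensive improvement and not an error in the plan. The retention measures, as written, target a set of 165 items (157 without the CSQ-8) and give the 20-item primary outcome no protection of its own. On assumed rates (25% missing, a quarter to a half recovered), the imputed share of primary outcomes falls from 25% to about 12.5–19%, and two-sided observed-case power at d = 0.60 rises from 0.83 to 0.86–0.89. At 35% missing, power goes from 0.78 to 0.83–0.87; at 15% the change is small (0.88 to 0.89–0.90). The size of the gain cannot be established from the document. The case rests on replacing some imputed primary outcomes with observed ones, not on rescuing power.

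**What to change.** Add one step at the end of the existing sequence: in the last e-mail (21 days) and in the telephone call, offer participants who decline the full set a link to the IAT alone. Include these scores in the primary intention-to-treat analysis and record their actual completion date.

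The cost is one short online form and revised wording for one e-mail and the call. A few participants may choose the short form and give no secondary outcomes; offering it only at the end limits this. The scores will also come late: if the reminder days run from the due date, an IAT returned after the last e-mail is at least 3 weeks past the 7-week point, which is why the date must be kept. The Abstract describes the trial as still recruiting, so at that date the change could reach participants not yet at T2.

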## Conclusion

To conclude, this internet- and mobile-based intervention is a treatment that aims to reduce disease burden of IUD in the general population. To complement research on IUD and to advance evidence-based treatment options, RCTs evaluating treatments for IUD are needed. Internet- and mobile-based interventions might be an appropriate strategy to overcome low treatment availability. This study will contribute to empirical research on IUD and provide information about their acceptability and efficacy. If the efficacy of this intervention can be established, the effectiveness of the intervention needs to be evaluated with regard to large-scale implementation in routine care to make the intervention available to a large number of affected individuals irrespective of place and time.

## Ethics Statement

This study has been approved by the ethics committee of the Friedrich-Alexander University Erlangen Nürnberg (no. 54_18 B). Written informed consent will be obtained from the participants of our study.
